However, larger randomised-controlled trials involving very old individuals beyond 80 years applying structured exercises are rare. Particularly machine-based exercises have not extensively been investigated in this patient cohort on a large scale. Moreover, the setting of senior care facilities seems to be ideal for introducing exercise interventions. On the basis of our pilot study (bestform-F; 77 residents; 74–103 years, 85.6 ± 6.6 years; 78% women) that has shown feasibility of a multimodal machine-based strength, balance and endurance training, [22] we have designed the “Bestform-trial – Best Function of Range of Motion”; hereinafter referred to as “bestform”, to examine the efficacy of this training on physical function and risk of falls as well as assessing safety of the intervention. The training programme is performed over a 6-month period in at least 20 senior care facilities in a cluster-randomized setting. The primary endpoint is the Short Physical Performance Battery (SPPB) after 6 months.

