## Methods/design

### Design and participants

The prospective cluster-randomised, controlled, two-armed study is organised and conducted by the Department of Prevention and Sports Medicine (Technical University of Munich, Germany). The participating senior care facilities (≥ 10 intervention senior care facilities,  ≥ 10 control senior care facilities) are randomly allocated to one of the two study groups. The participants of the intervention senior care facilities are provided with a physical training programme (“bestform-training”). The participants of the control senior care facilities will not receive any training intervention (usual care), but are provided with information meetings/brochures on a healthy lifestyle. In each intervention senior care facility a machine-based exercise training equipment is installed after randomisation.

The hypothesis of the bestform-trial is that a 6 months multimodal exercise training (machine-based strength, coordination and endurance training) is superior to usual care regarding Short Physical Performance Battery (SPPB) in residents aged ≥ 65 years living in senior care facilities. Secondary endpoints are outlined in Table 2 and obtained on site at three different time points: at baseline, after three months, and after six months. Afterwards, follow-up data will be collected after 18 and 30 months by questionnaires. The study flowchart is illustrated in Fig. 1. Our study protocol is in line with the SPIRIT 2013 statement for clinical trial protocols [23] and subsequent trial reporting considers the CONSORT recommendations for clinical trial reporting [24].

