### Secondary outcomes

Furthermore, secondary outcomes are:Change in SPPB after 3 months as compared to baselineChange in balance ability, mobility and risk of falling after 3 and 6 months as compared to baseline, measured by the Timed-Up-and-Go-Test and by stability tests on a balance platformChange of the 6-Minute-Walk-Test after 3 and 6 months as compared to baselineChange in handgrip strength after 3 and 6 months as compared to baselineMortality and rate of hospitalization over 6 monthsNumber of falls and fall-related injuries over 6 months, assessed by questionnaireChange in fear of falling (short FES-I), quality of life (WHO-5), nutritional status (MNA®-SF), risk screening for sarcopenia (SARC-F), physical activity and activities of daily living (Barthel-Index) recorded by questionnaires after 3 and 6 months as compared to baselineChange in fat free mass after 3 and 6 months as compared to baseline, measured by bioelectrical impedance analysisChange in calf and upper arm circumference after 3 and 6 months as compared to baselineChange in diastolic and systolic left ventricular myocardial function after 6 months as compared to baselineChange in proBNP after 3 and 6 months as compared to baselineChange in cognition after 6 months as compared to baseline measured by the MoCA

Further secondary endpoints are recruitment rate, adherence, drop-out and lost-to-follow-up rate as well as follow-up evaluation of SAEs, MACE, falls and fall-related injuries, and care degree after 18 and 30 months (Table 2).

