### Adverse and serious adverse events

The process evaluation comprises the documentation of recruitment rate and drop-out as well as lost-to-follow-up rate, the documentation of adherence to the training, and the documentation of adverse events (AEs) due to training (complaints while and immediately after training) and serious adverse events (SAEs).

AEs are defined as: Clinical events that occur during the training session or may possibly be related to the training intervention including accidents that occur during the training session or may possibly be related to the training intervention.

SAEs are defined as death, life-threatening events, events that lead to permanent damages or invalidity, or events that are followed by over-night hospitalisation.

AEs due to training and SAEs that occur during the study period irrespective of group assignment are documented in safety forms and transferred to a safety data base. In case of an SAE the principal investigator is directly informed and the procedure on further participation of the study determined e.g. study end, adaptations of the training, temporary or complete cessation of the training.

Throughout the course of the bestform trial, SAEs can be differentiated according to cardiovascular events and analysed separately. MACE are cardiovascular death, non-fatal stroke, and non-fatal myocardial infarction (3-point MACE). MACE and all-cause mortality will be documented during the study and the follow-up phase.

A questionnaire for falls documentation is used at the examinations ex1-ex3, in which the falls and fall-related injuries of the participants are recorded (Additional file 1: Supplement). A falls diary is not applied. Additional documentation is carried out by staff of the senior care facilities or by the trainers in the intervention care facilities (Table 2).

All participants are followed until end of study. A list of SAEs is provided to the responsive Ethics Committee after the end of the study.

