Secondary endpoints will be analysed in an exploratory manner. For continuous data, observed means and standard deviations will be presented for both study groups and tests for group differences will be performed as described for the primary analysis. Absolute and relative frequencies for both groups will be presented for binary outcomes. Group comparisons will be conducted by fitting marginal logistic regression models with study group as independent variable to the data accounting for within cluster correlations (generalised estimating equation, GEE models). For count data (e.g. number of falls) corresponding Poisson regression models or negative binomial models will be used. Kaplan–Meier curves will be drawn to illustrate distributions of time-to-event data (time to first MACE) for both study groups. For group comparisons, a Cox regression model with fixed effect for study group and robust standard errors considering the clustering will be fitted to the data. Estimated hazard ratios with corresponding 95% confidence intervals will be presented. Observed adverse events and serious adverse events will be listed and frequencies of adverse events and serious adverse events will be presented. Proportions of individuals with at least one adverse event will be compared between study groups using a logistic GEE model accounting for clustering.

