A key point of the bestform-training is the supervised training in small groups. Supervision is particular important for older adults, who often have comorbidities, in order to implement an individualised approach and to ensure that the training strain is adequate for the participants, but also safe. A review analysing adherence of older people to training programmes shows a generally higher adherence in supervised programmes [64]. The current World falls guidelines for fall prevention also recommend supervised exercises in care homes [21]. In addition to these aspects, a prescribed functional face-to-face therapy and other more everyday movements (e.g. chair gymnastics) should not be neglected. Furthermore, the group approach strengthens the social exchange and connectedness between the participants. Besides family members, friends also have a great influence on older people’s activity behaviour and group support can encourage regular training [65].

Limitations in this age group of old and very old individuals include a higher morbidity and mortality rate, as well as difficulties performing the training itself, a close monitoring and potential limitations due to cognitive impairments. These issues will also be documented and analysed for future exercise prescriptions.

With the bestform- training programme and its novel setting approach – to apply a machine-based training on site within a senior care facility—we expect a significant mean difference in change in physical function between seniors in the intervention and those living in control care facilities after six months. Particular safety aspects will be assessed in relation to efficacy of the training. The results of the study will contribute to a better knowledge of physical activity concepts for older adults, particularly those living in senior care facilities.

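### Kaplan–Meier curves for time to first MACE leave no place for non-cardiovascular death as a competing event, so absolute MACE risks read from them would be too high, noticeably so only if they run to 30 months

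*Protocol article*

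**What the plan says.** The paragraph on secondary endpoints in the protocol article's Statistical analysis section names Kaplan–Meier as the estimator and MACE as the endpoint: "curves will be drawn to illustrate distributions of time-to-event data (time to first MACE) for both study groups". For the comparison of arms, "a Cox regression model with fixed effect for study group and robust standard errors considering the clustering will be fitted to the data", with hazard ratios and 95% confidence intervals reported. The same paragraph makes all secondary analyses exploratory.

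The section Adverse and serious adverse events gives the event definition: "MACE are cardiovascular death, non-fatal stroke, and non-fatal myocardial infarction (3-point MACE". It adds that "MACE and all-cause mortality will be documented during the study and the follow-up phase".

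On duration, Design and participants says, after describing the assessments up to six months: "Afterwards, follow-up data will be collected after 18 and 30 months by questionnaires". Secondary outcomes lists MACE among the later items: "as well as follow-up evaluation of SAEs, MACE, falls and fall-related injuries, and care degree after 18 and 30 months".

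On the population, the Background describes the pilot cohort ("bestform-F; 77 residents; 74–103 years, 85.6 ± 6.6 years; 78% women"), and the Discussion concedes: "Limitations in this age group of old and very old individuals include a higher morbidity and mortality rate". Nothing in the article mentions competing risks, cumulative incidence functions or any specific handling of non-cardiovascular death in this analysis.

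**The concern.** Cardiovascular death is part of the composite; death from cancer, infection or injury is not. Such a death ends the possibility of a later MACE, so it is a competing event and not a loss of information. Kaplan–Meier with that death censored estimates the MACE risk in a hypothetical population in which nobody dies of anything else. If one minus the curve is read as the proportion of residents who have a MACE, it overstates that proportion whenever non-cardiovascular deaths occur.

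In a cohort of this age, possibly followed to 30 months, such deaths will not be rare. The Discussion treats safety as an important part of the case for introducing the training in care facilities, and MACE is the only endpoint that the article names for a time-to-event display. If training also changed non-cardiovascular mortality, the vertical gap between the two curves would no longer equal the difference in actual MACE risk.

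**Working it through.** **The plan's own figures.** The article states no MACE risk, event count or power, so there is none to reproduce. Its one calculated figure is the sample size, and from its stated 100 per group that holds: design effect 1 + (25 − 1) × 0.025 = 1.6; 100 × 1.6 = 160 per group; 320 / 0.8 = 400. It does not bear on this point.

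**Inputs.**
- From the article: estimator, event definition, and time points of 6 months (T = 0.5 years) and 30 months (T = 2.5 years).
- Assumed, because the article gives no rates: MACE rate m of 2–10 and non-cardiovascular death rate d of 5–25 per 100 person-years, both constant over time.

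**Formulas.**
- Kaplan–Meier with competing deaths censored: 1 − KM = 1 − exp(−mT).
- Actual risk (cumulative incidence, the Aalen–Johansen target): CIF = m/(m + d) × [1 − exp(−(m + d)T)].

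For any d above zero, the first exceeds the second.

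**Worked case, 30 months, m = 0.05, d = 0.10.** 1 − KM = 1 − exp(−0.125) = 11.8%. CIF = (0.05/0.15) × [1 − exp(−0.375)] = 10.4%. The excess is 1.3 points (from unrounded values), or 13% relative.

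**30 months, MACE rate 5 per 100 person-years (1 − KM = 11.8% throughout):**

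| Non-CV deaths per 100 person-years | CIF | Excess, points | Excess, relative |
|---|---|---|---|
| 5 | 11.1% | 0.7 | 6% |
| 10 | 10.4% | 1.3 | 13% |
| 15 | 9.8% | 1.9 | 19% |
| 20 | 9.3% | 2.5 | 26% |
| 25 | 8.8% | 3.0 | 34% |

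**Extremes of the assumed ranges.**
- 30 months, m = 2, d = 5: 4.9% against 4.6%, an excess of 0.3 points (6%).
- 30 months, m = 2, d = 25: 4.9% against 3.6%, an excess of 1.2 points (34%).
- 30 months, m = 10, d = 25: 22.1% against 16.7%, an excess of 5.5 points (33%).
- 6 months, m = 10, d = 25: 4.9% against 4.6%, an excess of 0.3 points (6%). This is the largest 6-month excess in the range; the smallest relative excess there is about 1%.

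**Effect on the gap between arms.** Suppose both arms have m = 5, but non-cardiovascular deaths run at 10 in one arm and 15 in the other. At 30 months both Kaplan–Meier curves stand at 11.8%, while the actual MACE risks are 10.4% and 9.8%, about 0.6 points apart. This needs a mortality difference for which the article gives no figure.

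**The case against.** Several limits on the point are sound.

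- **The censoring rule is inferred.** The article does not say how non-cardiovascular deaths enter the curves, and an analysis plan that is not shown might. But the article does name the estimator, and with this event definition censoring is what Kaplan–Meier ordinarily does. That is enough to raise the point, not to state the rule as fact.
- **The horizon is inferred.** No time span is given for the curves. Collection of MACE at 18 and 30 months makes the longer span the natural reading; if only six months were plotted, the matter would be trivial.
- **The curves are illustrative.** A reader might infer that the trial will publish inflated MACE proportions at 18 and 30 months. The article promises no such figures. It promises curves, hazard ratios, and frequencies of adverse and serious adverse events, and crude frequencies do not carry this particular bias.
- **The treatment comparison stands.** A reader might also infer that the Cox analysis is wrong. It is not: with competing deaths censored it estimates the cause-specific hazard ratio. That ratio does not by itself give a difference in MACE risk if other mortality differs by arm.
- **The size depends on assumptions.** With 30 non-cardiovascular deaths per 100 person-years and a MACE rate of 10, the 30-month excess would reach 40% relative (22.1% against 15.8%). But that death rate alone implies 1 − exp(−0.15) = 13.9% of residents lost to non-cardiovascular death by six months. This sits uneasily with the plan's allowance of about 20% without six-month data for all reasons, and with its selection of residents who can stand independently and pass a medical examination.
- **Sampling error is larger in the middle of the range.** With about 200 per arm, the 95% half-width around 11.8% is 1.96 × √(0.118 × 0.882 / 200) = 4.5 points before clustering and censoring, against a bias of 1.3 points. That argues for modest severity. It does not justify keeping an estimator whose error always runs in one direction.

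**Conclusion.** The point holds in limited form. Kaplan–Meier is the wrong estimator for the absolute risk of an endpoint that excludes non-cardiovascular death. If those deaths are censored, the direction of the error is certain: any MACE risk read from the curves is too high. Only its size is uncertain, because it rests wholly on assumed, constant rates. Within the ranges used it is negligible at 6 months and possibly material at 30 months, where it runs from 0.3 to 5.5 percentage points.

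The cause-specific comparison, the primary SPPB analysis and the sample size are unaffected. Severity is low to moderate: this is an inexpensive improvement to an exploratory safety analysis.

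**What to change.** In the secondary-endpoint paragraph of the Statistical analysis section:

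1. Replace the Kaplan–Meier curves for time to first MACE by Aalen–Johansen cumulative incidence curves per arm, with non-cardiovascular death as the competing event.
2. Keep the Cox model with cluster-robust standard errors and label its hazard ratio as cause-specific.
3. Show the cumulative incidence and the cause-specific hazard ratio for non-cardiovascular death beside it.

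The cost is about one sentence of text, a standard software call, and one extra curve and hazard ratio to report. No new outcome has to be collected: all-cause mortality is already documented in both phases, and the MACE definition already requires cardiovascular deaths to be told apart from other deaths.

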#### Usual care

Study participants in the control senior care facilities receive usual care and will not be involved in any aspects of the bestform-training. Instead, the participants are offered 1–2 information meetings by trained study personnel or information brochures on the topic of “Healthy Ageing” during the six months study period.

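### The planned between-group test of adverse events uses an AE definition tied to training that control residents never receive, so this one safety contrast is either not estimable or tilted against the intervention

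*Protocol article*

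**What the plan says.** Three parts of the protocol article bear on this.

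- **Definition and collection** (Adverse and serious adverse events). AEs are "Clinical events that occur during the training session or may possibly be related to the training intervention", with accidents of the same kind included. The process evaluation covers "the documentation of adverse events (AEs) due to training (complaints while and immediately after training) and serious adverse events (SAEs"). On scope: "AEs due to training and SAEs that occur during the study period irrespective of group assignment are documented in safety forms". SAEs are defined without reference to training: "SAEs are defined as death, life-threatening events, events that lead to permanent damages or invalidity, or events that are followed by over-night hospitalisation".
- **Exposure** (Usual care). Control participants "will not be involved in any aspects of the bestform-training".
- **Analysis** (Statistical analysis, paragraph on secondary endpoints). AEs and SAEs are to be listed and their frequencies presented, each named separately. Then: "Proportions of individuals with at least one adverse event will be compared between study groups using a logistic GEE model accounting for clustering". No corresponding test is named for the proportion with at least one SAE.

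**The concern.** A between-group comparison of proportions needs an event that can occur, and be recorded, in both arms. Here the event is defined by exposure to the treatment under test. A control resident has no training session in which an event could happen and no training to which one could be related.

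The contrast would therefore reflect the definition rather than compare safety with usual care. Safety is a stated aim, and the Discussion makes wider implementation conditional on the programme being shown safe and effective. A very large odds ratio with a tiny p-value, produced by an empty control cell, would be awkward to explain once reported. The protocol itself fixes both the definition and the test, so an analysis plan that follows it faithfully inherits the conflict.

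**Working it through.** **Inputs.** The article gives no expected AE or SAE rate and no power for this comparison. Its only sample-size figure concerns the primary endpoint, and it reproduces: a difference of 1 point with SD 2.5 needs 99 per group (stated 100); design effect 1 + (25 − 1) × 0.025 = 1.6; 100 × 1.6 = 160 per group; 320 / 0.8 = 400 in total. I take 200 per arm from 400 at 1:1. This is an assumption, since randomisation is by facility.

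**Reading A: AEs exclude SAEs.**

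1. The control proportion is 0/200 by definition. For any intervention proportion p above 0, the log odds ratio is log[p/(1 − p)] − log[0/1], which is infinite. The control arm is all zeros and the intervention arm is mixed, so this is quasi-complete separation.
2. A logistic GEE was fitted to simulated data with 20 clusters of 20 and control events fixed at zero. With 8 intervention participants having an AE, the group coefficient ran to 24.4 with robust SE 0.31. With 16, it ran to 25.1 with SE 0.24. The printed p-value was 0, the software reported convergence, and the intercept's SE was often undefined. The failure can thus pass for a highly significant result.
3. To show how few events would look like harm, take Fisher's exact test. With equal arms of n and no control events, the two-sided p is 2 × C(n, k) / C(2n, k). At n = 200:

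| Intervention participants with an AE (k) | p |
|---|---|
| 5 (2.5%) | 0.061 |
| 6 (3%) | 0.030 |
| 10 (5%) | 0.0017 |

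With 160 per arm, 6 events again give p = 0.030. These figures are illustrative only: they ignore clustering, and Fisher's test is not the planned analysis. The empty control cell does not depend on them.

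**Reading B: AEs include SAEs.**

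Let s be the SAE risk, equal in both arms, and a the risk of a non-serious training AE, independent of SAEs and possible only in the trained arm.

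- Control odds: s / (1 − s).
- Intervention odds: (s + a − sa) / [(1 − s)(1 − a)].
- Ratio: 1 + a / [s(1 − a)].

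| s (assumed) | a (assumed) | Odds ratio with no SAE difference |
|---|---|---|
| 10% | 3% | 1 + 0.03/0.097 = 1.31 |
| 10% | 10% | 1 + 0.10/0.090 = 2.11 |
| 20% | 3% | 1 + 0.03/0.194 = 1.15 |
| 20% | 10% | 1 + 0.10/0.180 = 1.56 |

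The ratio exceeds 1 whenever a is above 0. The model can be estimated on this reading, but the contrast is tilted against the intervention.

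**The case against.** The best defence has four parts.

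- **SAEs may be meant to count as AEs.** They are ordinarily a subset, both kinds of event go into one safety database, and the test sentence does not exclude them. This stands in part. It removes the zero cell, the infinite odds ratio and the Fisher figures. It leaves the asymmetry of reading B, and the sentence just before the test names AEs and SAEs separately.
- **Events are documented whatever the group.** This does not help. The clause says whose events are documented. An AE must still be due to training, so the clause has practical effect only for SAEs.
- **Safety against usual care is compared elsewhere.** This stands. Mortality and hospitalisation over 6 months are secondary outcomes, falls and fall-related injuries are recorded by questionnaire, and MACE and deaths are documented throughout. The statistical section provides logistic GEE for binary outcomes, count models for falls and a Cox model for time to first MACE. A reader might infer that the trial has no valid safety comparison, or that only SAEs are recorded alike in the two arms. The article supports neither.
- **Secondary endpoints are exploratory.** Also true. The primary SPPB analysis and the sample size are untouched.

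Nor is the intervention-arm AE count worthless. Events in trained residents are real and useful for describing the programme. What lacks meaning is the contrast with an arm in which they cannot arise.

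**Conclusion.** The AE definition, the untrained control arm and the between-group AE test do not fit together, and the test is wrong as written. On the more literal reading, the control count is zero by definition, the odds ratio has no finite estimate, and the result can only be null or unfavourable to the intervention. If SAEs are counted, the test is estimable but biased in the same direction, with odds ratios of about 1.2 to 2.1 under the assumed rates and no true SAE difference.

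The stronger claim, that the control arm is zero on any reading, is not supported, because it depends on SAEs not counting as AEs. The fault is limited to one non-primary safety test. It matters mainly because this is the only test the article names for AEs or SAEs as such. The AE and SAE rates and their independence are my assumptions.

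**What to change.** Change the wording of the protocol and the analysis plan before analysis:

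1. Drop the between-group test of training-related AEs. Report them descriptively for the intervention arm: participants with at least one AE, and a rate per sessions attended.
2. Apply the clustered logistic GEE instead to the proportion with at least one SAE, which is defined without reference to training and documented in both arms.
3. State whether an SAE also counts as an AE in the listings and frequency tables.
4. For any between-group comparison of falls, use only the questionnaire given in both arms. Leave out trainer reports, which exist only in intervention facilities.

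The cost is a few sentences. No new data are needed: SAEs and falls questionnaires are already collected in both arms, and the instructors already document adherence, which supplies the denominator for the rate.
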